### Participants

People living in the 72 selected wards in Morang district are eligible to participate when they are over 18 years old and understand and speak Nepali. Inclusion criteria to be eligible for the trial are (1) answering affirmative to the heart-mind screener and for functional impairment [30] and (2) scoring above 16 on the WHO Disability Assessment Schedule for functional impairment (WHODAS) [31]. The heart-mind screener is locally developed (sensitivity of 0.94) and will be used to determine the acceptability of local idioms of distress and impairment due to these problems [30]. The WHODAS is a generic instrument assessing health and disability that can be used with adult populations across cultures. Additionally, only males will be eligible for enrolment in the 14 “male” wards and, similarly, only females will be eligible for enrolment in the 58 “female” wards. Exclusion criteria for participation in the trial are (1) presence of a severe mental disorder (e.g., psychosis) or cognitive impairment identified by a score above 2 on an adapted version of the WHO Ten Questions Screen (TQS) for disability detection [32] and (2) alcohol use disorder (score > 16 on the alcohol use disorders identification test (AUDIT)).

Imminent risk of suicide will be determined through a structured screening questionnaire. Persons with current suicidal ideation and suicide plans or recent attempts will be referred immediately to a psychosocial counselor but will not be excluded from participating in the study. Observable symptoms of psychosis and severe cognitive impairment will be assessed using an observation checklist. Four items are included to examine the client’s ability to comprehend questions and follow basic instructions, and the degree to which the client can communicate with the assessor. A positive response above 2 on any of these behavioral items is an indication for exclusion and is discussed with a supervisory team. Alcohol dependency will be assessed by the alcohol use disorders identification test (AUDIT) [33]. According to WHO’s guidelines for AUDIT use in primary care, people that score below 16 can benefit from simple advice [34]. Those with a score of 16 or over would benefit the most from advice plus brief counseling and continued monitoring and, therefore, those that score 16 or above on the AUDIT will be excluded from the study and referred to a nearby mhGAP-trained health professional [10] .

### Procedures

Each ward of participating municipalities in Morang district will have one community informant (CI) who will conduct recruitment through the use of the Community Informant Detection Tool (CIDT) and community sensitization activities. CIs are often Female Community Health Volunteers (FCHVs), mothers’ group members, or social mobilizers within their respective communities. CIs will, as much as possible, also be gender-matched for the “gender” of their wards. CIs from intervention and control wards will be trained separately to maintain blinding. Control ward CIs will not be given any information on Group PM+ or any other information about the existence of an intervention arm. Intervention CIs will additionally be given a 1-day training to become Group PM+ ‘helpers’ for the sessions.

The CIs will be trained on the CIDT to identity people with common mental disorders in the community. The CIDT is a pro-active case detection approach aimed to increase help seeking using a vignette-based tool designed for the ease of use by lay people. It has been developed and tested in Nepal [35], with positive results on the positive predictive value (0.68) and increasing the utilization of mental health services [36]. A general distress CIDT version had been adapted for this trial [28], which includes gender-matched vignettes for the “gender” of the wards.

After the community informant identifies a person in the community who matches the symptoms described in the vignettes, they will be asked if they would like support for their problems. If so, the research assistant (RA) will then conduct the consent and screening procedures.

People who are identified as meeting the exclusion criteria initially by the RAs will be referred to health workers trained in mhGAP, hospitals with psychiatric services, or counselors. People that meet the inclusion criteria for the study, in both the intervention and control wards, will receive a visit from the CI for a family meeting. Based on the preference of the participants, this can either be with or without their family. After the family meeting, RAs will conduct the baseline assessment with enrolled participants. Once baseline is completed, only those in the intervention group will be contacted by CPSWs to inform them about Group PM+. After all participants in an intervention ward have been contacted by the CPSW, Group PM+ sessions will start.

### Informed consent

The consent procedures consist of two steps, first informed consent for screening and then informed consent for participation in the Group PM+ trial [10] . After identification by the CI, potential eligible people will be approached by the research assistant for informed consent for screening. If a participant screens positive, the CI will give more information about the research project and will conduct the full trial informed consent during the family meeting.

All respondents who decide to participate will provide written consent, if possible. Full information on the study will be provided in local, lay Nepali language before obtaining consent from each participant. Given high rates of illiteracy, the consent form will be read to all participants. After providing verbal consent, literate participants will be asked to acknowledge the process with a signature. For illiterate participants, verbal consent or adding a symbol or sign will be sufficient. We will make sure that potential participants fully understand what participation entails and that they, at any time and without any consequences, can withdraw their consent without having to give an explanation.. Participants will be made aware that refusal to participate will not have an impact on any type of support they receive outside the study. For the qualitative interviews, separate written informed consent will be taken at the time of the interview.

### Outcome measures

#### Primary outcomes

The primary outcome is levels of individual psychological distress, measured by the GHQ-12 [37, 38], at endline, 20 ± 1 weeks after baseline for the control arm participants, and 12 + 1–2 weeks after the time of the final group session for the Group PM+ arm participants. The GHQ-12 consists of 12 questions that are scored on a four-point Likert scale ranging from 0 to 3, with higher total scores representing higher levels of distress. The GHQ-12 has been translated and clinically validated in Nepal (cut-off 1/2, sensitivity 85.6%, specificity 75.8%, positive predictive value (PPV) 86.7%, negative predictive value (NPV) 84%) [39].

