**Methods/design:**

This c-RCT will compare Group PM+ to enhanced usual care (EUC) in participants with high levels of psychological distress recruited from the community. The study is designed as a two-arm, single-blind c-RCT that will be conducted in a community-based setting in Morang, a flood affected district in Eastern Nepal. Randomization will occur at ward level, the smallest administrative level in Nepal, with 72 enrolled wards allocated to Group PM+ or to EUC (ratio 1:1). Group PM+ consists of five approximately 2.5-h sessions, in which participants are taught techniques to manage their stressors and problems, and is delivered by trained and supervised community psychosocial workers (CPSWs). EUC consists of a family meeting with (a) basic information on adversity and mental health, (b) benefits of getting support, (c) information on seeking services from local health facilities with mhGAP-trained staff. The primary outcome measure is levels of individual psychological distress at endline (equivalent to 20 ± 1 weeks after baseline), measured by the General Health Questionnaire (GHQ-12). Secondary outcome measures include levels of functioning, depressive symptoms, post-traumatic stress disorder symptoms, levels of social support, somatic symptoms, and ways of coping. We hypothesize that skills acquired will mediate any impact of the intervention.

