### Design and setting

The study is designed as a two-arm, single-blind c-RCT that will be conducted in a community-based setting in Morang, a flood-affected district in Eastern Nepal. Outcomes will be measured on participants’ level at baseline and at two additional time points, midline and endline. Midline is 7 weeks after baseline (for the Group PM+ participants, this will be approximately 1 week after concluding the intervention). Endline is 20 ± 1 weeks after baseline for the control arm participants, which is approximately 12 + 1–2 weeks after the time of the final group session for the Group PM+ arm participants. Endline is the primary endpoint for the study.

Administrative levels in Nepal are: (1) provinces; (2) districts; (3) *nagarpalikas* or *gaupalikas* (municipalities or rural municipalities); and (4) wards. Randomization will occur at the ward level, the smallest administrative level in Nepal, with half of 72 enrolled wards receiving Group PM+ and the other half receiving EUC. Importantly, given that the groups of the Group PM+ intervention will be of a single gender (see details below in “Group PM+ intervention” section) and that we do not have resources to enroll more than one group per ward, we will select a subset of 14 of the 72 wards to be those where we enroll male participants and the remaining 58 wards will enroll female participants. This fraction (14/72), close to 20% of all wards, was selected to reflect the anticipated uptake of services, which was expected to be lower in this region than in studies conducted by our team in other regions [15, 16]. Further, we note that the selection of 14 wards will not be random but instead those 14 wards will be selected to be 14 wards that are close together and that are, nevertheless, representative of the types of wards in the study region. More specifically, we selected these 14 “male” wards close together so that we can best use resources of the male personnel trained to deliver to the Group PM+ intervention. Because of the sub-selection of “male” and “female” wards, randomization will be stratified by gender and will account for several other baseline cluster-level covariates using restricted randomization (see details below in the “Randomization and sample size” section).

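### The primary endpoint is timed from baseline in control but from the final session in Group PM+, with no rule for which clock governs if delivery slips by more than a week or two

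*Protocol article*

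**What the plan says.** Endline is the primary time point, and the protocol article describes it in three ways.

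- **By arm.** Objectives, Sample size justification and Primary outcomes use two clocks. The last of these sets endline at 20 ± 1 "weeks after baseline for the control arm participants", and at 12 + 1–2 "weeks after the time of the final group session for the Group PM+ arm participants".
- **In common.** The Methods/design part of the abstract gives a single definition without a split by arm: "endline (equivalent to 20 ± 1 weeks after baseline".
- **As approximately the same visit.** Design and setting gives the control timing and adds: "which is approximately 12 + 1–2 weeks after the time of the final group session for the Group PM+ arm participants".

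Midline is fixed to baseline in both arms: "Midline is 7 weeks after baseline (for the Group PM+ participants, this will be approximately 1 week after concluding the intervention". The planned final session is therefore near week 6.

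Procedures sets the order of events in intervention wards: "After all participants in an intervention ward have been contacted by the CPSW, Group PM+ sessions will start". No maximum interval from baseline to first or final session is stated. In Statistical analyses, time enters the primary model as an indicator for midline or endline, not as weeks elapsed.

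**The concern.** The PM+ clock starts at a delivery event that happens after randomization and has no counterpart in control. If sessions slip, the text followed literally moves endline in one arm only. A PM+ interview at week 22 or 23 and a control interview at week 20 would then enter the model as the same visit.

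The resulting error is the change in mean GHQ-12 in the PM+ arm over the extra weeks. If scores are still falling, through natural recovery or regression to the mean after selection on distress and impairment, a later PM+ visit flatters the intervention. If scores are rising, through a waning effect, general worsening or season, it counts against the intervention. Either way, a timing difference would be read as a treatment effect on the primary outcome.

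**Working it through.** **Stated power first.** Inputs from Sample size justification: 72 wards (36 per arm), 8 enrolled and up to 2 lost, so 6 analysed per ward, ICC 0.2, SD 7, difference 3.2 (effect size 0.46), two-sided 5%.

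- Design effect = 1 + (6 − 1) × 0.2 = 2.0.
- Effective n per arm = 36 × 6 / 2.0 = 108.
- Standard error = 7 × √(2/108) = 0.95.
- Power (normal approximation) = 92.2% for 0.46 and 91.9% for 3.2/7. With a t distribution on 70 df, 91.5% and 91.2%.

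The claim of at least 90% is reproduced, and it does not depend on the timing of endline.

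**Timing.** Planned final session = 7 − 1 = week 6. PM+ endline = 6 + delay + 13 to 14 weeks, reading 12 + 1–2 as 12+1 to 12+2. An alternative reading is 12 to 14 weeks. The control window is weeks 19–21, midpoint 20. The gap is the PM+ midpoint minus 20.

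| Delay (weeks) | PM+ window, 13–14 | Gap | PM+ window, 12–14 | Gap |
|---|---|---|---|---|
| 0 | 19–20 | −0.5 | 18–20 | −1.0 |
| 0.5 | 19.5–20.5 | 0 | 18.5–20.5 | −0.5 |
| 1 | 20–21 | 0.5 | 19–21 | 0 |
| 2 | 21–22 | 1.5 | 20–22 | 1.0 |
| 3 | 22–23 | 2.5 | 21–23 | 2.0 |
| 4 | 23–24 | 3.5 | 22–24 | 3.0 |

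On the first reading the PM+ window lies wholly inside the control window up to a delay of 1 week, touches it only at week 21 at 2 weeks, and is disjoint beyond 2 weeks. On the second reading it is disjoint beyond 3 weeks.

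**Size of the possible bias.** The document gives no rate of change in GHQ-12 over follow-up. As an assumption, take 0.05 to 0.3 points per week, linear. For a 3-week delay in every PM+ ward on the first reading:

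- Bias = 2.5 × 0.05 to 2.5 × 0.3 = 0.125 to 0.75 points.
- Relative to target = 0.125/3.2 to 0.75/3.2 = 4% to 23%.
- Relative to the standard error = 0.13 to 0.79, which gives a two-sided type I error of about 5.2% to 12.3% instead of 5%.

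On the second reading the gap is 2.0 weeks: 0.1 to 0.6 points, or 3% to 19% of the target. With no drift the bias is zero.

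**Partial delay.** If only 6 of 36 PM+ wards ran 3 weeks late, the mean delay would be 6 × 3 / 36 = 0.5 week, and on the first reading the average gap would be zero.

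**The case against.** The best defence is that the article means one visit. The abstract defines endline once for both arms, and Design and setting presents the session-based timing as a rough equivalent of 20 weeks from baseline. On the planned schedule this is true, and PM+ is even measured about half a week earlier on average. This stands, and it reduces the defect to a missing rule: the text does not say which clock wins when the two part.

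A reader might infer that any delivery delay biases the comparison. The table does not support that: up to about a week of delay leaves PM+ inside the control window.

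A reader might also infer that late finishes are likely, because sessions wait until everyone in the ward has been contacted and 12 facilitators serve 36 groups. The article does not say so. That is about three groups per facilitator (36/12), it is not stated that these run one after another, and Procedures gives an order of events, not a delay. Trial status also limits slippage: 25 November 2018 to 31 May 2019 is 187 days, or 26.7 weeks. A ward with baseline on the opening day and a PM+ endline otherwise due by week 20 could absorb at most 26.7 − 20 = 6.7 weeks if that completion date holds, and later wards less. So long delays are bounded, but delays above 2 weeks are not excluded.

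Finally, a fixed interval after treatment answers a legitimate question about durability. That is a reason to record the interval. It does not justify timing one arm of a randomized comparison by a clock that the other arm lacks.

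**Conclusion.** The point holds as a conflict in the definition of the primary time point. Three sections define it by arm, the abstract defines it in common, Design and setting treats the two as approximately equal, and no text says which governs. Followed literally, the arm-specific definition lets delivery timing shift follow-up in PM+ only, and the model does not correct for it.

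The article does not show that the comparison is biased. Bias needs both an average PM+ delay of more than about a week and a GHQ-12 mean that is still changing around week 20, and its direction is not known in advance. Under the assumed drift of 0.05–0.3 points per week and a 3-week delay throughout the PM+ arm, it would be about 0.13–0.75 points (4–23% of the 3.2-point target). It is zero without drift.

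**What to change.** Use one anchor throughout: endline at 20 ± 1 weeks after baseline in both arms, scheduled regardless of the date of the final session. Bring the abstract, Objectives, Design and setting, Sample size justification and Primary outcomes into line with it. This matches the abstract and the way midline is already timed.

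Report actual weeks from baseline to endline by arm, and keep weeks since the final session as a descriptive variable for PM+. Add a sensitivity analysis of the primary outcome, either restricted to interviews within weeks 19–21 or using elapsed weeks. Because elapsed time is itself measured after randomization, this analysis supports the common anchor and does not replace it. If interviews have already taken place, the reporting and the sensitivity analysis can still be done.

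The cost is wording and interview scheduling. The downside is a somewhat shorter post-treatment interval for groups that finish late. Sample size and power do not change.

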#### Secondary outcomes

Secondary outcomes include levels of depressive symptoms measured by the Primary Health Questionnaire (PHQ) [40]; general functioning measured with the WHO Disability Assessment Scale (WHODAS) [31]; post-traumatic stress disorder (PTSD) symptoms measured by the Post-traumatic stress disorder Check List (PCL-5) [41]; levels of perceived social support measured by the Multi-dimensional Scale of Perceived Social Support (MSPSS) [42]; and the Somatic Symptom Scale 8 (SSS-8) [43]. Please see Table 2 for an overview of the different measures on different time-points (Table 3).

**Table 2 Tab2:** Quantitative outcome measures

Construct	Instrument	Description	Assessment time periods			
			Enrollment(−***t***_***1***_)	Baseline (t_0_)	Midline (t_1_)	Endline (t_2_)
***Screening (participants)***						
Daily functioning	*WHODAS*	Participants rate their ability to engage in daily activities	X			
General psychological Distress	*Heart-mind*	Participants note if they have had any *“man ko samasya”* or heart-mind problems recently	X			
Alcohol use disorder	*Alcohol Use Disorders Identification Test (AUDIT)*	Participants rate alcohol use and associated behavior, as well as daily ethanol consumption	X			
Suicidality	*Suicidality*	Participants rate if they have recently had suicidal thoughts, ideation, and plans	X			

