***Secondary outcomes (participants)***						
Depression symptoms	*Depression symptoms (PHQ)*	Participants rate depression symptoms over past two weeks		X	X	X
Daily functioning	*WHODAS*	Participants rate their ability to engage in daily activities		X	X	X
Post-traumatic stress symptoms	*PTSD Checklist for DSM5 (PCL-5)*	Participants rate their post-traumatic stress symptoms on a scale		X	X	X
Perceived social support	*Multidimensional Scale of Perceived Social Support (MSPSS)*	Participants assess their own connectedness with close family, friends and other forms of support		X	X	X
Somatic symptoms	*Somatic Symptom Scale-8 (SSS-8)*	Participants rate how much they have been bothered by somatic symptoms		X	X	X
General psychological distress	*Heart-mind*	Participants note if they have had any *“man ko samasya”* or heart-mind problems recently			X	X

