### Ethical considerations

Throughout the different study phases participants in both arms will have access to mhGAP-trained health staff in the districts. When necessary they will be referred to a specialist for further assessment or management of severe psychiatric problems. If a participant experiences psychological problems after the project, they will be offered additional support.

All adverse events (AEs) and serious adverse events (SAEs) that are reported spontaneously by the participant or observed by either research or intervention staff will be recorded. All staff will be trained in the TPO Nepal Adverse Events Reporting Mechanism, which guides the process of reporting and supporting/referral in case of any adverse events.

All AEs and SAEs will be reported to a local independent Data Safety Management Committee (DSMC). The DSMC includes psychiatrists, non-governmental organization experts in psychosocial programs, and researchers and is established specifically for oversight of the trial and review of SEs and SAEs. The chair or a nominated person from the DSMC will review SAEs within 48 h, deciding if an SAE is likely related or unrelated to the intervention. The DSMC will review all AEs once a month. In both instances the committee will, where necessary, determine any appropriate action in respect of ongoing trial conduct (i.e., referral to specialized care). All changes in treatment resulting from AEs or SAEs will be reported to the DSMC in Nepal. TPO Nepal is responsible for data collection and storage and making data available to the DSMC, funders, and IRBs for audits when appropriate.

The project has been approved locally by the Nepal Health Research Council, Kathmandu, Nepal and by the WHO Ethical Review Committee (version 3; protocol ID 2817, October 25, 2018).

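### People at known suicide risk may be enrolled, but the suicidality questionnaire is scheduled only at enrolment, leaving follow-up to passive capture that is likely to differ between arms

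*Protocol article*

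**What the plan says.** On entry, the Participants section states: "Imminent risk of suicide will be determined through a structured screening questionnaire". People found to have current ideation and plans, or a recent attempt, "will be referred immediately to a psychosocial counselor but will not be excluded from participating in the study".

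Table 2 places the suicidality measure in its screening block: "Participants rate if they have recently had suicidal thoughts, ideation, and plans". The only mark is in the enrolment column. Suicidality is absent from the secondary outcomes, both in the text and in the table.

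On timing, Design and setting states: "Midline is 7 weeks after baseline" and "Endline is 20 ± 1 weeks after baseline for the control arm participants".

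Three other provisions apply after enrolment:

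- **Adverse events (Ethical considerations).** Events are recorded if the participant volunteers them or if staff notice them. The Data Safety Management Committee (DSMC) receives them, with SAEs reviewed within 48 h and all AEs monthly.
- **Referral (Enhanced usual care; Ethical considerations).** Both arms can be referred when needed to a primary care worker trained in mhGAP, and suicidality is given as an example. Of the period after the trial, the article says: "If a participant experiences psychological problems after the project, they will be offered additional support".
- **PHQ (Table 2; Secondary outcomes).** "Participants rate depression symptoms over past two weeks", at baseline, midline and endline. The article does not describe the items or any step that follows from an answer.

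**The concern.** The trial identifies a risk group at the door, chooses to keep it, and then schedules no repeat of the instrument that identified it. Two things are at stake.

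The first is what the trial can report. The Background and the Discussion link its result to release of the group manual for wide use. On its own suicidality measure, the trial could not say whether suicidality rose, fell or stayed level under Group PM+ compared with EUC.

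The second is fairness of the comparison. If suicidality reaches the record only when volunteered or noticed, the arm that staff see more often will tend to yield more reports at the same true frequency. The two arms are not seen equally often.

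**Working it through.** The plan gives no figure on this point, so the check sets the relevant sections side by side.

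**1. Is the single assessment a stated schedule or just abbreviated text?** The four instruments in the screening block of Table 2 compare as follows:

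| Instrument | Enrolment | Baseline | Midline | Endline |
|---|---|---|---|---|
| WHODAS | X | X | X | X |
| Heart-mind | X | – | X | X |
| AUDIT | X | – | – | – |
| Suicidality | X | – | – | – |

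The table lists a screening instrument again when it is carried forward, as it does for WHODAS and heart-mind. It does not do so for suicidality. AUDIT also stops, but people above its threshold are excluded, whereas people positive on suicidality are kept. The dedicated measure is thus used at 1 of 4 time points and at 0 of 2 follow-up visits; the PHQ is used at 3 of 4.

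**2. Do the other provisions measure suicidality?**

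- AE and SAE recording depends on disclosure or observation. Ideation may be neither volunteered nor visible. DSMC review acts only on what has been recorded.
- Referral when needed is a response; it schedules no question that would reveal the need.
- The PHQ is planned as a symptom score and, at baseline, as a subgroup cut-off. With its items undescribed, the article supports neither the claim that it covers suicidality nor the claim that it does not.

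**3. Is passive capture equal between arms?** Study contacts described for all participants after baseline:

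- Group PM+: 5 sessions + 2 assessments = 7 contacts for a full attender. Sessions last 2.5 to 3 h, so 5 × 2.5 = 12.5 to 5 × 3 = 15 h with staff. A distress rating (SUDS) is taken in sessions 2 to 5, a supervisor observes at least two sessions per group, and helpers follow up those who miss one.
- EUC: 2 assessments. The family meeting comes before baseline and is given in both arms.

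From midline to endline, 20 − 7 = about 13 weeks, neither arm has a scheduled contact for all participants. Qualitative interviews reach only a subsample.

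**4. Consequence for the comparison.** Let s₁ and s₀ be the probabilities that an event is recorded in Group PM+ and in EUC. Then

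recorded risk ratio = true risk ratio × (s₁ / s₀).

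With s₁ > s₀, the likely direction given step 3, Group PM+ looks worse than it is, or a true reduction is hidden. The document gives neither s₁ nor s₀, so the size of the distortion cannot be computed.

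**The case against.** The strongest reply has four parts.

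- **The risk is not left without provision.** AEs and SAEs are recorded in both arms by staff trained in a named reporting mechanism, the DSMC reviews them, and referral for suicidality is open to both arms. This stands. A reader might infer from Table 2 that suicidality goes wholly unmeasured for 20 weeks, or that a flagged person is never asked again. The documents do not support that. They show only that no repeat of this questionnaire is scheduled.
- **The PHQ might show suicidal thoughts.** It might; the article does not describe the items, so this cannot be settled in either direction. No use of the PHQ for this purpose is stated.
- **This is a condensed article.** Table 3, the schedule, could not be read for this review, and the full protocol may contain further procedures. That limits certainty. But Table 2 sets out measures by time point and does show which screening instruments continue, so the single mark is a stated schedule and not mere silence.
- **Nothing here contradicts itself; a screening tool is used for screening.** True of the schedule. The point is a design weakness, arising because those who screen positive are kept in the trial.

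It would also be tempting to attach a number of people affected. The article gives no prevalence or incidence of suicidality, so any such count would rest on chosen rates and is not offered.

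**Conclusion.** The point holds in a limited form. People with current suicidal ideation and plans or a recent attempt may be enrolled, and the dedicated questionnaire is scheduled at neither follow-up visit. Suicidality is therefore not systematically reassessed on that instrument, and what the article describes in its place is passive.

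Because Group PM+ has five staffed sessions and EUC has no comparable contact after baseline, capture is probably more complete in Group PM+, and a comparison of this harm between arms could be biased. The direction is a reasoned expectation and the size is unknown.

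The conclusion assumes that Table 3 agrees with Table 2 and that the full protocol adds no repeat assessment. The primary GHQ-12 analysis is unaffected. This is a worthwhile, inexpensive improvement, not a flaw that invalidates the trial.

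**What to change.** In Table 2, and in Table 3 if it agrees, add the existing suicidality questionnaire at midline and endline for all participants in both arms, asked by the blinded research assistants. Report the proportion positive by arm at each visit, descriptively, as a safety result. If Table 3 or the full protocol already schedules this, correct Table 2 to match.

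The investigators must also reconcile two statements: the Participants section sends people at suicide risk to a psychosocial counselor, while the Enhanced usual care section names an mhGAP-trained primary care worker for suicidality. Which applies, and what follows a positive answer, is for the plan to settle; no clinical rule is proposed here.

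Cost: slightly longer interviews at two visits that already take place, equally in both arms, and a protocol modification reported through the channels named under Trial status. No new instrument, visit or assessor is needed. The burden is a fair consideration, since the plan shortened the PCL-5 to limit it.
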